### Interventions

Patients in the study and control groups undergo a mixed-type abdominoplasty, also known as anchor-line abdominoplasty, based on a previously published procedure [42], under general anaesthesia, coordinated by the same surgeon for all the operations.

Both the study group and the control group are instructed to maintain, postoperatively, routine vitamin and mineral supplementation for post-bariatric patients, ensuring that the supplement Materna® (Wyeth Laboratory, Markham, ON, Canada), which contains 60 mg of iron, 1 mg of folic acid and 12 μg of vitamin B_12_, among other elements, is taken daily after breakfast.

Patients in the study group receive intravenously, during the immediate postoperative period, 200 mg of ferric hydroxide saccharate (Takeda Pharma Ltd., Berlin, Germany) diluted in 200 mL of saline over 60 minutes. The same dose is administered on the first postoperative day post-bariatric abdominoplasty, totalling 400 mg of intravenously administered iron supplementation for each patient in the study group. The iron is administered by the nursing team as specifically recommended for the administration of intravenous iron, with monitoring of vital signs and possible adverse reactions [43].

Patients in the control group receive an additional postoperative orally administered supplementation of iron through the ingestion of one tablet of 330 mg of iron (III)-hydroxide polymaltose complex (equivalent to 100 mg of elemental iron) after lunch and another after dinner. Patients in the control group are instructed to maintain this additional orally administered iron supplementation during the 8-week follow-up period (Fig. 1).

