#### Allergic reactions

Allergic reactions to the use of intravenously administered iron are rare, and severe adverse effects have been reported only at doses above 400 mg [30]. In the case of an allergic reaction, the medication is suspended immediately, and the event is reported as an adverse event.

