### Interventions – concomitant care

All patients are discharged on the second postoperative day and provided with prescriptions of antibiotics (cefadroxil, 500 mg orally 12/12 h), analgesics (dipyrone, 1000 mg orally 6/6 h) and anti-inflammatory drugs (celecoxib, 200 mg orally 12/12 h) for use during the first postoperative week. Suction drains are removed when drainage is less than 50 mL in 24 hours. A restrictive practice was adopted for blood transfusions, in which none of the patients receive blood transfusion while their Hb levels remain above 7 g/dL [51].

Patients receive a list with nutritional guidelines that advise them to eat six times per day, chew their food well, avoid fatty foods and sweets and include fruits and vegetables in their diet. The use of other food or vitamin supplements is not permitted other than those recommended by the study during follow-up.

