#### Adverse effects

Adverse effects will be estimated by measuring the differences between the two groups in regards to the proportions of mild (grades 1 and 2) and severe (grade 3, 4 and 5) adverse effects, which are possibly, probably, or definitely related to the use of iron supplementation during the follow-up period. Version 4 of Common Terminology Criteria for Adverse Events (CTAE v4.0) [54] will be used to grade adverse effects. The following adverse effects will be considered mild: transitory development of a skin rash, itching, tachycardia, tremor, dyspepsia, constipation, and nausea with improvement after discontinuation of medication or of symptomatic treatment. The following adverse effects will be considered severe: the maintenance of symptoms even after discontinuing the medication and treatment, need for hospitalisation, bronchospasm, anaphylactic shock and death. At each visit, patients will be asked about adverse events that have manifested since their previous visit. A standardised list containing the most common adverse effects of iron supplementation will be used. Cases where there is a need to definitively discontinue use of the medication will be considered treatment failures.

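### Active adverse-reaction monitoring on days 0–1 is described only for the IV infusions, so the between-arm comparison of mild, transitory adverse effects is at risk of detection bias (minor, secondary outcome only)

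*Protocol article*

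**What the plan says.** The Adverse effects section makes the difference between groups in the proportions of mild and severe effects an outcome, counting those at least possibly related to iron over the follow-up period. It gives one ascertainment rule without distinction of arm: "At each visit, patients will be asked about adverse events that have manifested since their previous visit". One instrument serves both arms: "A standardised list containing the most common adverse effects of iron supplementation will be used". Table 1 puts the timepoints at 1, 4 and 8 postoperative weeks. The effects classed as mild are "transitory development of a skin rash, itching, tachycardia, tremor, dyspepsia, constipation, and nausea", when they improve after stopping the drug or with symptomatic treatment.

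The Interventions section adds a second route in the study-group paragraph. The two 60-minute infusions, one immediately after surgery and one on the first postoperative day, are given by nurses "with monitoring of vital signs and possible adverse reactions". Under Allergic reactions, which concerns IV iron, "In the case of an allergic reaction, the medication is suspended immediately, and the event is reported as an adverse event". The control-group paragraph describes the tablets and no monitoring, and does not give the day on which they start. Both arms are in hospital over this period: "All patients are discharged on the second postoperative day". Under Blinding, patients and researchers know the allocation; only the surgeon who assesses local complications does not.

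**The concern.** An effect that is brief, or that shows only when someone takes a pulse or looks at the skin, has two chances of being recorded in the IV arm: during an infusion, and at the week-1 question. In the oral arm the only chance written down is the week-1 question. Tachycardia, tremor, itching, rash and nausea in the first two days can also follow anaesthesia, analgesics or blood loss in either arm. Because staff are unblinded, a sign seen during an infusion is easily judged possibly related to iron. Equal true rates could then yield more recorded mild effects in the IV arm. The same distortion could offset part of a real gastrointestinal excess on oral iron. No later analysis can recover events that were never recorded, so this has to be settled at data collection.

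**Working it through.** The protocol states no adverse-effect rate or detection probability, so there is no figure of its own to reproduce on this point. The one usable number is 28 women per arm (Sample size section). It reproduces: a two-sided 5% t test with 80% power, a difference of 1.5 g/dL and an SD of 1.84 needs 24.6, so 25 per arm, and 25 / 0.9 = 27.8, so 28.

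**Model, with equal true rates in both arms.** All four inputs are assumptions.

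- p: proportion of women with a countable effect on days 0–1
- s: share picked up by the week-1 question, the same in both arms
- f: share of these effects that fall in infusion hours
- m: share of effects in those hours that monitoring detects, taken as 0.9

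Recorded in the oral arm: p·s. Recorded in the IV arm: p·[s + (1 − s)·f·m]. The spurious IV excess is p·(1 − s)·f·m. It cannot be negative, and it is zero when s = 1.

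The last column is the chance that an uncorrected two-proportion z test at two-sided 5% is significant with 28 per arm, by exact binomial enumeration.

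| p | s | f | IV recorded | Oral recorded | Excess (points) | Significant |
|---|---|---|---|---|---|---|
| 0.10 | 0.5 | 0.25 | 6.1% | 5.0% | 1.1 | 3% |
| 0.20 | 0.7 | 0.25 | 15.4% | 14.0% | 1.4 | 5–6% |
| 0.20 | 0.5 | 0.25 | 12.3% | 10.0% | 2.3 | 6% |
| 0.20 | 0.5 | 0.50 | 14.5% | 10.0% | 4.5 | 8–9% |
| 0.40 | 0.3 | 0.25 | 18.3% | 12.0% | 6.3 | 10% |
| 0.40 | 0.3 | 0.50 | 24.6% | 12.0% | 12.6 | 22% |
| any | 1.0 | any | p | p | 0 | about 5% |

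Example: 0.40 × (1 − 0.3) × 0.50 × 0.9 = 0.126.

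**How much time is monitored.** Two infusions of 60 minutes make 2 hours. Taking the stay as roughly 48 hours, 2/48 is about 4%. If effects were spread evenly over the stay (f = 0.042), even p = 0.40 with s = 0.3 gives 0.40 × 0.7 × 0.042 × 0.9, about 1 point, and 5–6% significance. The 2–13 point range needs effects to cluster around the infusions. That is plausible immediately after surgery, but the protocol does not establish it.

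**Eight-week endpoint.** A woman who has another recorded effect later counts anyway. If a proportion q do so, independently of days 0–1 and equally in both arms, the excess shrinks by the factor (1 − q). With q = 0.2 to 0.4, 12.6 points becomes 12.6 × 0.8 = 10.1 to 12.6 × 0.6 = 7.6.

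**The case against.** The strongest reply is that much of the asymmetry is inferred from silence. This is a condensed article, every woman is an inpatient after general anaesthesia, and nothing says that control patients go unobserved. Ward recording may well be in the full protocol. That stands: one can say only that active monitoring is described for one arm, not that it is absent in the other.

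A reader might infer two sharper contrasts, and neither is supported. The first is that the oral arm is asked later: both arms are first asked at week 1, with the same list and the same look-back. The second is that IV reactions are reported immediately: in "the medication is suspended immediately, and the event is reported as an adverse event" the adverb belongs to suspending the drug, and the rule covers allergic reactions only. The article does not say whether other infusion findings enter the comparison.

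The relatedness filter also counts against large figures. A symptom put down to anaesthesia or blood loss is not an event for this outcome, so p may be well below 20–40%. The filter is not full protection, because the judgement is unblinded and the threshold is only possible relatedness.

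Finally, infusions need monitoring and some reactions occur only by that route, so part of the asymmetry is inherent. This limits the remedy. Removing reactions found only during infusion from the main comparison, or restricting it to events after discharge, would drop genuine IV harms while keeping eight weeks of oral gastrointestinal effects. That would bias the comparison in favour of IV iron.

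**Conclusion.** The point holds as a risk of detection bias towards more recorded mild effects in the IV arm, confined to days 0–1. Visit questioning is the same in both arms for the whole eight weeks. The size cannot be established from the protocol. Under the stated assumptions (p 20–40%, recall 30–50%, 25–50% of effects in infusion hours, 90% monitoring detection) it is about 2–13 points, with a 6–22% chance of a nominally significant result when the true rates are equal. With 70% recall at p = 20% and f = 25% it is about 1 point, and with complete recall it is nil. Later events dilute it further.

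A reader might infer that the comparison is simply biased and can support no tolerability conclusion. A calculation that lets every day 0–1 symptom be caught at 90–95% by monitoring in the IV arm, against 30–50% by recall in the oral arm, does give an excess of 8–24 points and 14–57% significance. That needs essentially all symptoms to fall in about 2 monitored hours, applies no relatedness filter and looks at days 0–1 alone. The protocol supports none of these.

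Severity is minor. The outcome is secondary, and haemoglobin at week 8 is not touched.

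**What to change.** In the Adverse effects section:

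1. For women still to be enrolled, have existing ward staff complete the same standardised adverse-effect list and vital-sign record at the same inpatient times in both arms. By August 2015, 19 of the planned 56 had undergone surgery, so up to 56 − 19 = 37 could be covered from that date.
2. Report adverse effects for the inpatient window (days 0–2) and the post-discharge window (weeks 1, 4 and 8) separately, as well as overall.
3. State that all infusion reactions count in the overall IV-arm safety figure. Flag those found only through infusion monitoring, and add a sensitivity comparison without them.
4. State in the report that ascertainment on days 0–1 may have been unequal for women already treated. If the full protocol or ward records show equivalent recording in the oral arm, say so instead.

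The cost is one short extra inpatient checklist and one more table. Treatment, visits and sample size do not change.

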**Fig. 1 Fig1:**
[figure not shown]
Trial flow diagram

### Interventions – modifications

#### Gastrointestinal upset

Iron polymaltose has a lower incidence of adverse effects than other ferrous salts [44]. However, patients are instructed to take the iron orally after meals to minimise gastrointestinal effects of the medication. Patients who report gastrointestinal symptoms may reduce the supplement dose to one tablet per day.

#### Allergic reactions

Allergic reactions to the use of intravenously administered iron are rare, and severe adverse effects have been reported only at doses above 400 mg [30]. In the case of an allergic reaction, the medication is suspended immediately, and the event is reported as an adverse event.

### Interventions – adherence

#### Adherence reminder sessions

Face-to-face reminder sessions as to the importance of treatment adherence occur the day before surgery and at each postoperative return appointment [45]. Such sessions include:The importance of following medical recommendations on the use of medications. In addition, to facilitate adherence, recommendations on the ingestion of medications are associated with the patients’ daily activities, specifically their mealsClear instructions, in writing and verbally, are provided for all prescriptions and, after asking whether the patient has any questions, the patient is asked to repeat the instructions in their own words

#### Adherence assessments

Two indirect methods to measure patient adherence are used: the Morisky-Green test (MGT) [46–48] and the Haynes-Sackett test [49, 50]. The MGT consists of four questions: (1) ‘Do you ever forget to take your medicine?’, (2) ‘Are you careless at times about taking your medicine?’, (3) ‘When you feel better, do you sometimes stop taking the medicine?’, (4) ‘Sometimes, if you feel worse when you take the medicine, do you stop taking it?’ An affirmative response to any one of these questions classifies the individual as non-adherent. The Haynes-Sackett test consists of the following statement and question: ‘Many people have some kind of problem with taking their medication. In the last 30 days, have you had difficulties with taking your medication?’ An affirmative response classifies the individual as non-adherent. Both methods are used during each patient’s return visit to quantify adherence to treatment.

### Interventions – concomitant care

All patients are discharged on the second postoperative day and provided with prescriptions of antibiotics (cefadroxil, 500 mg orally 12/12 h), analgesics (dipyrone, 1000 mg orally 6/6 h) and anti-inflammatory drugs (celecoxib, 200 mg orally 12/12 h) for use during the first postoperative week. Suction drains are removed when drainage is less than 50 mL in 24 hours. A restrictive practice was adopted for blood transfusions, in which none of the patients receive blood transfusion while their Hb levels remain above 7 g/dL [51].

Patients receive a list with nutritional guidelines that advise them to eat six times per day, chew their food well, avoid fatty foods and sweets and include fruits and vegetables in their diet. The use of other food or vitamin supplements is not permitted other than those recommended by the study during follow-up.

### Outcomes

#### Primary outcome measures

The primary outcome is the detection of a minimum difference of 1.5 g/dL in the final mean values of Hb levels at the eighth postoperative week between the study and control groups.

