**Methods/Design:**

In this multicentre open-label randomised clinical trial, 56 adult women undergoing post-bariatric anchor-line abdominoplasty will be allocated at a ratio of 1:1 for postoperative supplementation with two intravenously administered applications of 200 mg of iron saccharate or postoperative supplementation with 100 mg of iron polymaltose complex administered orally, twice a day for 8 weeks. The primary outcome is the difference in mean haemoglobin levels between the two groups at eight postoperative weeks. Secondary outcomes evaluated at one, four and eight postoperative weeks include iron profile, reticulocyte count, overall quality of life measured using the Short-Form 36 Health Survey (SF-36) questionnaire, fatigue measured using the Functional Assessment of Chronic Illness Therapy – Fatigue (FACIT-F), adverse effects and postoperative complications.

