### Objectives

#### Primary objective

To assess whether iron saccharate supplementation intravenously administered in two 200-mg doses during the perioperative period of post-bariatric anchor-line abdominoplasty results in an increase in Hb levels in the eighth postoperative week (study group) compared to orally administered iron supplementation (control group).

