	Allocation: randomised
	Masking: unblinded
	Assignment: parallel
	Purpose: treatment
	Phase: not applicable
Date of first enrolment	April 2014
Target sample size	56
Recruitment status	Recruiting
Primary outcome	Haemoglobin level increase in the eighth week of postoperative abdominoplasty after bariatric surgery, measured by automated haematology counter in g/dL
Key secondary outcomes	Presence of iron deficiency assessed by serum ferritin, postoperative haemoglobin levels, fatigue measured by the Functional Assessment of Chronic Illness Therapy – Fatigue (FACIT-F) questionnaire, quality of life measured by the Short-Form 36 Health Survey (SF-36), adverse events, surgical complications. Timepoints: 1, 4 and 8 postoperative weeks

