### Sample size

A sample size of 56 patients (28 per group) was calculated, assuming an 80 % statistical power to detect a minimum difference in Hb levels of 1.5 g/dL (the primary outcome), considering a standard deviation for Hb levels of 1.84 [61], a two-tailed significance level of 0.05 and a patient loss to follow-up of 10 %.

The need for postoperative follow-up assessments of participants, the relatively brief 8-week follow-up period, the flexibility to decrease the iron oral dose to one tablet daily for patients reporting gastrointestinal symptoms, and reminder sessions for treatment adherence might reduce participant attrition and, consequently, the attrition bias.

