### Blinding

Due to the nature of the intervention (orally administered iron supplements result in blackening of the stool [62], facilitating the identification of the allocation group), we chose not to blind the patients or researchers to the allocation group. However, the surgeon who evaluates the incidence of local complications is blinded to the allocation group. In addition, the patients are not informed about the outcome of their laboratory tests to prevent the knowledge of their test results from influencing their responses on the quality of life questionnaires [63]. The use of an objective laboratory measurement as the primary endpoint (Hb level) also reduces detection bias.

Although unmasked clinical trials are subject to performance bias, the disclosure of allocation concealment at the end of the surgery reduces the possibility of surgical team performance bias during surgery. In addition, both the recommendation to use the same vitamin and mineral supplementation and the written supply of the same nutritional guidelines for all participants aim to reduce performance bias over the postoperative follow-up period.

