### Statistical methods

#### Statistical methods – outcomes

The data will be entered into the statistical software Statistical Package for the Social Sciences (SPSS), version 17.0, and initially evaluated descriptively using summary measures (means, standard deviations, minima, maxima, and quartiles). To guarantee reliability and avoid selective outcome reporting, a fully specified statistical analysis plan will be written before unmasking.

To analyse the behaviour of variables for quality of life, Hb level, reticulocyte count, iron profile and CRP level at different times, a repeated measure analysis of variance (ANOVA) will be employed. This model will presuppose the normality of the data tested in the residuals (difference between the observed and estimated value) of the fitted model using the Kolmogorov-Smirnov test.

To determine the presence of an interaction between group and time, the means of the variables between groups will be compared at each time-point using Student’s *t* test for independent samples, and means between different time-points for each group will be compared using Student’s *t* test for paired samples.

For those variables in which there is a lack of normality in the data, non-parametric Mann-Whitney tests will be performed to compare the differences between groups at each time-point, and the Wilcoxon test will be used to compare patterns over time for each group. Bonferroni correction will be used for these tests to ensure an overall significance level of 5 %.

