### Statistical methods: additional analyses

#### Adjusted analyses

The final mean Hb levels in the eighth postoperative week (primary outcome) will be adjusted for baseline Hb level, ferritin levels, and TSI via an analysis of covariance (ANCOVA). Both the adjusted and unadjusted analyses will be reported in the final publication.

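### The 1.5 g/dL planning difference is worded as the primary outcome, the outcome variable differs between sections, and the planned baseline-adjusted ANCOVA is only an additional analysis

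*Protocol article*

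**What the plan says.** The protocol article describes the primary outcome in several places, and they do not agree.

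- **Outcomes section, on the primary measure:** it reads "The primary outcome is the detection of a minimum difference of 1.5 g/dL in the final mean values of Hb levels". The time-point named there is week 8, and the Discussion repeats the definition.
- **Sample size:** 80% "statistical power to detect a minimum difference in Hb levels of 1.5 g/dL (the primary outcome", with the parenthesis closing there. The label again attaches to the 1.5 g/dL difference.
- **Abstract, Methods/Design:** "The primary outcome is the difference in mean haemoglobin levels between the two groups at eight postoperative weeks". There is no threshold. The Adjusted analyses section likewise attaches the label to final mean Hb at week 8.
- **Table 1, Primary outcome:** "Haemoglobin level increase in the eighth week of postoperative abdominoplasty after bariatric surgery". The Primary objective also speaks of an increase.

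On analysis, the Adjusted analyses section sits under the heading for additional analyses. It plans an ANCOVA of week-8 Hb on baseline Hb, ferritin and transferrin saturation index (TSI), and adds: "Both the adjusted and unadjusted analyses will be reported in the final publication". Neither is given priority.

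On timing, Statistical methods – outcomes promises that "a fully specified statistical analysis plan will be written before unmasking". The Blinding section says "we chose not to blind the patients or researchers to the allocation group", and Allocation: implementation has the envelope opened at the end of each operation.

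**The concern.** An outcome is a variable measured on each patient. The 1.5 g/dL is the between-group difference used to size the trial. Writing one as the other leaves open whether an observed difference below 1.5 g/dL would count as success.

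The variable also shifts between the week-8 value and the increase. Under randomisation both have the same expected between-arm difference. Compared without adjustment, however, they have different variances and can give different p-values, and the planning SD is stated for Hb levels.

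An ANCOVA that includes baseline Hb gives the same treatment estimate for either variable, so it removes that ambiguity. It is already planned with named covariates, yet it ranks as additional.

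The analysis plan is the stated protection against selective reporting. Its deadline is an event that occurs patient by patient, starting with the first operation. Trial status reports 19 patients operated on by August 2015, while the plan is still described in the future tense.

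**Working it through.** **Inputs from the Sample size section:** difference 1.5 g/dL, SD 1.84, two-sided alpha 0.05, power 80%, loss 10%, 28 per group.

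**1. The plan's own figure.**
- Normal approximation: n per arm = 2 × [1.84 × (1.960 + 0.842) / 1.5]² = 23.6, so 24.
- Exact t test: 24.6, so 25.
- Allowing for loss: 25 / 0.90 = 27.8, so 28 per arm and 56 in total.

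The stated size is reproduced. It is that of an unadjusted two-sample t test on week-8 Hb at the full 0.05. Power with 25 evaluable per arm is 80.6%.

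**2. Literal threshold.** The smallest significant observed difference, if the observed SD is 1.84, is

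t(0.975, 48) × 1.84 × √(2/25) = 2.011 × 0.520 = 1.05 g/dL.

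If the true difference is 1.5, the observed difference is symmetric about 1.5, so it reaches 1.5 with probability about 50%. A rule requiring an observed 1.5 would therefore have about 50% power.

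**3. Week-8 value versus increase, unadjusted.** SD of change = √(SD₀² + 1.84² − 2 × r × SD₀ × 1.84). Neither the baseline SD (SD₀) nor the correlation r is in the document; both are assumed. Power is for a true 1.5 with 25 per arm.

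| Assumed r | Change, SD₀ = 1.84 | Change, SD₀ = 1.0 | Week-8 value |
|---|---|---|---|
| 0.3 | 67% | 82% | 81% |
| 0.5 | 81% | 90% | 81% |
| 0.7 | 95% | 97% | 81% |

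**4. ANCOVA.** Residual SD = 1.84 × √(1 − r²), true difference 1.5, 25 per arm.

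| Assumed r | Residual SD | Power |
|---|---|---|
| 0 | 1.84 | 81% |
| 0.3 | 1.76 | 84% |
| 0.5 | 1.59 | 90% |
| 0.7 | 1.31 | 98% |

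These figures ignore the cost of fitting covariates. With three covariates and 50 patients, chance imbalance multiplies the variance by about (50 − 3)/(50 − 3 − 3) = 47/44 = 1.07. A simulation with that cost included gives about 78%, 82%, 88% and 97% when r is read as the joint multiple correlation. Break-even with the unadjusted test is at a joint R² of 1 − 44/47 = 6%, a multiple correlation of about 0.25.

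**The case against.** **The threshold was probably not meant.** The abstract and the Adjusted analyses section state the outcome without one. Trial design calls this a superiority trial, and the Sample size section treats 1.5 as the difference to detect at two-tailed 0.05. Nothing says that a smaller observed difference is a failure. This stands: a reader might infer that the trial really has 50% power, but the documents support that only under the literal wording of the Outcomes section.

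**The variable mismatch may be loose wording.** *Increase compared with oral iron* can simply mean higher Hb. A reader might take from the 67% figure that a change analysis would be badly underpowered. That figure needs a baseline SD of 1.84. Patients with Hb below 11.5 g/dL are not included, so the baseline SD may well be smaller, and at 1.0 the loss disappears.

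**The primary test may be named elsewhere.** The promised analysis plan is not shown and could name it, and the sample size already implies the unadjusted t test. A reader might conclude that the test will be picked after the results are seen, with an inflated error rate (6.3% to 8.1% in simulation if either the t test or the ANCOVA could count, at r from 0.3 to 0.7). The documents do not show that intention, and they commit to reporting both results.

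**The deadline still has some effect.** Even in an open-label trial, a plan fixed before outcomes are compared by arm constrains the analysis. It would be too strong to call the safeguard worthless; the defect is that the stated event does not give a date.

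**The ANCOVA gain is not proven.** It depends on correlations that the document does not give, and the entry limits on Hb, ferritin and TSI may weaken them. This also stands.

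**Conclusion.** The point holds as a defect of definition and ranking, not of sample size. Three sections word the planning difference as the outcome, two give week-8 Hb with no threshold, and Table 1 gives an increase. Only a literal reading of the Outcomes section turns significant differences of about 1.05 to 1.5 g/dL into failures and lowers power from about 81% to about 50%.

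Making the planned ANCOVA primary is well supported. It uses data already collected and settles week-8 value versus increase. By the simple formula it has 81% to 98% power over assumed correlations of 0 to 0.7. Allowing for three covariates, it loses two to three points of power if they explain nothing and gains once they explain more than about 6% of the variance. All these figures assume SD 1.84 and 25 evaluable patients per arm.

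The deadline *before unmasking* cannot be applied as written, because researchers know each allocation from the end of surgery.

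**What to change.** 1. Define the primary outcome as Hb (g/dL) at the eighth postoperative week. Align the Primary objective, Table 1, Primary outcome measures, Sample size and Discussion with it, and check the registry entry, which Table 1 only reproduces.
2. Describe 1.5 g/dL only as the sample-size assumption.
3. Make the planned ANCOVA (arm, baseline Hb, ferritin, TSI) the single primary analysis at two-sided 0.05, reporting the adjusted difference with its 95% CI. Label the unadjusted comparison supportive. Adding hospital as a covariate is optional.
4. Replace the deadline with: before any outcome data are tabulated by arm. Sign and date the analysis plan accordingly.

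The cost is wording in the protocol, the registry and the analysis plan, through the protocol's own amendment procedure where it applies. No extra patients, visits or assays are needed, and the sample size stays at 56.
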